## Methods/design

### Study design and setting

This study is a four-arm, randomized, placebo-controlled clinical trial in which participants get sham or real forms of two interventions, including EC and tDCS. It is aimed to investigate the effectiveness of EC, tDCS, and a combination of both on disgust reduction, clinical symptoms, and cognitive characteristics in C-OCD patients. Randomly assignment will be in blocks of 4 in 1:1:1:1 allocation to four parallel groups: (1) real EC plus real tDCS, (2) sham EC plus real tDCS, (3) real EC plus sham tDCS, (4) sham EC plus sham tDCS. We consider sham interventions to be able to separate the exposure effect from the EC effect and also to monitor the placebo effect. Assessments occur at baseline, after completion of 10 interventional sessions, and in a 2-month follow-up. All groups have similar assessments and equal intervention amounts (equal time, activity, and number of sessions). Figure 1 shows the design of the study. The trial will be conducted in the Cognitive Science Laboratory of Ferdowsi University of Mashhad, Mashhad, Iran.

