### Participants

Eligibility criteria include the following: aged 18–55 years; diagnosed with OCD based on The Diagnostic and Statistical Manual of Mental Disorders-Fifth Edition-Text Revision (DSM-V-TR) with significant contamination-based symptoms; sufficiently able to read, write, and do computerized tasks; being on stable medication for at least the last 3 months; and filling out the written consent.

The potential participants will be excluded if one or more of the following conditions are present: diagnosis of psychotic disorders or another comorbid with severe symptoms, alcoholism or drug abuse, a severe medical condition that may restrain the ability to engage in assessments and interventions, “Yes” answer to any items of screening questions for transcranial electric stimulation (tES) [43], invalid response on baseline tests.

Those participants who receive new medical prescriptions or other brain stimulations during the administering trial or follow-up durations will be excluded from further assessments or analysis.

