### Sample size

We calculated the sample size using the G*Power 3.1 software. To be able to get an effect on our primary outcomes (disgust feeling and clinical symptoms) in three measurements (pre-, post-, and follow-up) at repeated-measure-MANOVA approach, with 95% confidence and 80% power, estimating large effect size with Cohen’s *f* value 0.40, a sample size of 46 participants was calculated. With an attrition rate of 20%, we aim to enroll 55 participants.

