### Statistical analysis

First, data entry will be double-checked. Data quality will be examined regarding data distribution, and outliers will be excluded from further analysis. When these items are ensured, the primary and secondary outcomes will be analyzed in detail using IBM SPSS statistics 25 for Windows (Armonk, NY: IBM Corp). Descriptive statistics (e.g., mean and standard deviation) will be reported for each arm separately. We will conduct the analysis within the intention-to-treat (ITT) framework to investigate the effectiveness of the interventions for all subjects with multiple imputed data sets in case of missing data. The appropriate statistical method will be performed to analyze data. The major one will include mixed and repeated measures of multivariate analysis of variance (MANOVA) to assess the effect of group (arm) and time and their interactions on the result of EEG recordings, computerized tests, and self-report measures as dependent variables. The significant level will be set at 0.05. The covariates, including age, disgust sensitivity, anxiety, and depression, will be considered in the statistical model.

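### The exclusion for new prescriptions or other brain stimulation after randomisation is not reconciled with the promised intention-to-treat analysis of all subjects

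*Protocol article*

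**What the plan says.** Two statements in the protocol article decide who is analysed.

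- **Participants.** After the entry criteria, a separate sentence says that participants who "receive new medical prescriptions or other brain stimulations during the administering trial or follow-up durations will be excluded from further assessments or analysis". It covers both the treatment and follow-up periods, so it acts after randomisation. It does not restrict the kind of prescription.
- **Statistical analysis.** "We will conduct the analysis within the intention-to-treat (ITT) framework to investigate the effectiveness of the interventions for all subjects", and this is to be done "with multiple imputed data sets in case of missing data".

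Patients may enter on medication, the condition being "being on stable medication for at least the last 3 months". A change of treatment during the trial is therefore possible. On timing, the Study design section states: "Assessments occur at baseline, after completion of 10 interventional sessions, and in a 2-month follow-up". No section limits the exclusion to a per-protocol set, and none says that the excluded participants stay in the ITT set.

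**The concern.** ITT keeps every randomised participant in the arm assigned, whatever happens later. A rule that takes people out because of a later event gives up that protection if the event is related to response. A new OCD drug or another course of brain stimulation plausibly follows poor response. If so, more poor responders are lost from the less effective arm, that arm looks better than it was, and the estimated effect shrinks. If new treatment is unequal between arms for some other reason, the rule can create a difference where none exists.

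The two sentences can also define different analysis populations for both primary outcomes. If the choice is left until the data are seen, the result may depend on it.

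**Working it through.** **1. The plan's own figure.** The Sample size section gives 46 participants "with 95% confidence and 80% power", f = 0.40 and three measurements. The four arms make this a group-by-time test in repeated-measures MANOVA, with s = 2, df1 = 6, df2 = 2(N - 4) and noncentrality 0.40² × N × 2. At alpha 0.05 the smallest N is 46, with power 0.8015, so the figure reproduces. For the same test, power is 0.882 at N = 55, 0.779 at N = 44 (55 × 0.80) and 0.727 at N = 40. The article does not say whether its 20% attrition includes participants removed by this rule.

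**2. The two readings side by side.**

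| Reading of the Participants sentence | Fits ITT of all subjects? | Consequence |
|---|---|---|
| The participant leaves the analysis | No | Randomised people are dropped for a post-randomisation event |
| Only data after the event are not collected or used, then imputed | Yes, formally | A scheduled follow-up is given up and replaced by imputation |

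**3. Size under the first reading (complete-case deletion).** These inputs are assumptions: one two-level factor, 27 real against 28 sham (55 split in two), SD 1, higher score = worse, true effect 0.80 SD, two-sided t-test at 0.05. The chance of exclusion is 1/(1 + exp(-(a + b·y))), where y is the outcome, b is 1 or 2, and a is set to give the stated sham rate and is shared by both arms. There were 8,000 replicates.

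| Sham excluded | Estimate (SD) | Power |
|---|---|---|
| 0% | 0.80 | 83% |
| 5% | 0.75-0.78 | 79-81% |
| 10% | 0.71-0.76 | 75-78% |
| 20% | 0.65-0.73 | 68-72% |

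At 20% in sham, 8-11% of the real arm is excluded.

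**4. A check by hand.** Suppose everyone above a fixed severity cut c is removed. The mean of those who remain is μ - φ(c - μ)/Φ(c - μ). With 20% of sham removed, c = 0.842.
- Sham: 0 - 0.280/0.800 = -0.350.
- Real: -0.8 - 0.104/0.950 = -0.909.
- Difference: 0.909 - 0.350 = 0.56.

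With 10% removed (c = 1.282) the difference is 0.65. The direction is the same, and the loss is larger because the trigger is sharper.

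**5. No true effect, same logistic model.**

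| Excluded in the two arms | False positives |
|---|---|
| Equal | about 5% |
| 5% and 20% | about 7-10% |
| 5% and 30% | about 11-18% |

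The spurious difference favours the arm that loses more participants.

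**6. Size under the second reading.** The same 27 against 28 and a true effect of 0.80 were used. The event was driven by the post-treatment score, the correlation of post with follow-up was 0.7 (assumed), and follow-up was imputed from arm and post score. The estimate was about 0.80 at 10%, 20% and 30% sham exclusion, against about 0.66-0.77 for complete cases. This result requires the trigger to depend on scores already observed. If the event falls before the post-treatment assessment, only the baseline score is available, and it carries no information on response.

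**The case against.** A reader might infer that the two rules can never both be followed. The text does not force that. The word *further* can govern both nouns, so that earlier data stay in and later values become missing and are imputed. On that reading the plan estimates an effect without new co-treatment, a recognisable aim in a trial that requires stable medication. For the same reason, it is not established that an event during follow-up deletes valid baseline and post-treatment data. This part of the objection stands. What remains is that the article does not say which reading applies, and the second still gives up obtainable data.

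A reader might also take it as fact that exclusions are outcome-related. The article gives no reason for new prescriptions. The inference is reasonable for new OCD treatment and weak for unrelated drugs, which the unqualified wording also covers.

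The sizes are open to challenge too. The deletion figures use a two-group t-test without the planned imputation or MANOVA, and the exclusion rates are assumed. With three months of stable medication at entry, two weeks of sessions (10 at five a week) and a 2-month follow-up, high rates are not obvious. At 5% the loss is small. It is tempting to quote a false-positive rate of about 18%, but that is the upper end of one scenario. It needs 5% against 30% exclusion with no treatment effect, among participants blinded to allocation, and the documents support no such imbalance.

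**Conclusion.** The point holds as an unreconciled conflict between two stated rules on one natural reading, and as an avoidable loss of follow-up data on the other. An article may leave detail to a fuller document, but here it states both rules and they need to be made consistent.

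If exclusion means deletion, depends on outcome and affects 5-20% of sham participants, a true 0.80 SD is estimated at about 0.65-0.78 SD, and power falls from 83% to about 68-81%. With no true effect, the error rate is close to nominal unless exclusion differs clearly between arms. If later values are imputed from the participant's own earlier scores, and those scores explain the trigger, most of the bias goes. All of these sizes rest on assumed rates and models. The conflict in wording does not.

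**What to change.** Reconcile the Participants and Statistical analysis sections as follows.

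- Record any new prescription or other brain stimulation with its date and indication.
- Keep the participant in all scheduled assessments and in the primary ITT analysis, in the arm assigned.
- Confine the present exclusion to a labelled per-protocol or sensitivity analysis. For example, set values after a new OCD treatment to missing and impute them.
- Report the number of such events by arm.

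This concerns data collection and analysis only, not clinical care. It costs an amended sentence and one further analysis, and uses visits already scheduled. The downside is that the primary estimate then includes the effect of any new treatment. A sponsor who wants the effect without new treatment would find it in the sensitivity analysis. Where a follow-up has already been missed under the current rule, the analysis part can still be applied: keep the data that were collected and impute the rest.

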### Recruitment

Through a research agreement, several psychiatrists and psychotherapists will refer participants to the researchers. Study ads and flyers will be available in clinics for C-OCD patients as potential subjects. Self-referral will be another path. They will also be recruited via online advertising on social media as well as the distribution of the study ads and flyers among university students. Online advertisements and flyers provide some information about the trial and inclusion criteria. Interested candidates will be invited to an initial meeting and baseline assessment within 3 days of enrollment. Candidates informed by flyers or advertisements will also pass a diagnosis interview by a therapist at the first session to check full inclusion criteria.

### Material

The computerized tasks and training will be pictorial. The pictures should belong to one of three classes: (1) contamination-related pictures that elicit disgust, (2) pleasant pictures that elicit positive emotions such as joy or calmness, and (3) neutral pictures that elicit no particular emotion. We have collected a picture series from internet websites containing 30 pictures in each class. In collecting procedures, we dynamically screened pictures based on the comments and ratings of people other than the research team (healthy and OCD people). Ultimately, a collection of 90 pictures was selected (30 for each class). In a final pilot rating, a group of 15 patients with C-OCD symptoms was required to rate them on a scale from − 10 (very disgusting) to 0 (neutral; not disgusting-not pleasant) to 10 (very pleasant) to ensure their emotional value and significant differences between classes.

#### Conditioned stimuli

In a survey asking people with OCD about contamination concern-related situations and stimuli that elicit disgust and emotion, a list of items was obtained. It included good examples of stimuli to be targeted as CSs. Based on the list, we have collected pictures containing those stimuli. The pictures visibly contained the contamination about OCD people are experiencing concern or obsessions. It might be an exaggeration of real-life situations for some pictures. For example, OCD people show obsessions, “What if the toilet is not completely clean,” even if any dirtiness is obvious, and we had to select a picture of a really dirty toilet to elicit that emotion. These include 30 colorful pictures (e.g., a dirty hand, a muddy face, a pile of unwashed clothes, a dirty sink) rated between − 7.5 to − 10 (mean score= − 9.44) and will be applied in developing an EC training as CSs. Some will also be applied for cognitive tests as emotionally disgusting stimuli.

#### Unconditioned stimuli

Unconditioned stimuli will consist of pleasant pictures (positive-valence unconditioned stimuli; pUS), used in real EC training, or completely neutral (neutral-valence unconditioned stimuli nUS), used in sham EC training. The pUSs will be those 30 pleasant pictures selected in the picture-collecting procedure and rated between 7.5 to 10 in the pilot rating (mean score = 9.36). They are colorful pictures such as a smiling face, a cute baby, the nature of winter, spring, the sooth waves of the sea, and beautiful flowers. All can elicit positive emotions and not seem to be related to any compulsions. In contrast, the nUSs will include geometrical figures (e.g., circle, rectangular) or symbols (e.g., percent, omega), all in white color set on a black background.

#### Neutral stimuli

We have also provided several colorful pictures that do not elicit any particular emotions. The neutral collection includes 30 pictures rated from − 1.5 to + 1.5 (mean score = 0.92) in the pilot rating. They will be the neutral pictorial stimuli in cognitive tasks.

### Interventions

The interventions will comprise EC training and brain stimulation via tDCS.

EC training is a kind of emotion-focused associative learning. The valence of a CS may alter via pairing it with an emotionally valanced US. Recently, it has been proposed as a strategy for modifying emotional components in normal or clinical populations [44]. Fear and disgust are the most negative emotions targeted for such a strategy [24, 45], in which the stimuli that elicit fear or disgust pair with the US of positive valence. This pairing may decrease their negative valence, so feared or disgusting stimuli are experienced as less unpleasant than before. Based on the literature that implicates EC as potentiation for targeting disgust in OCD [25], we will administer an innovative EC paradigm with the details below, combined with or without brain stimulation using tDCS.

tDCS is a non-invasive brain modulation method that may change cortical excitability by applying a weak direct current between two electrodes (anode and cathode) positioned on the scalp. An increase or decrease in excitability is due to anodal or cathodal tDCS [46]. The dorsolateral prefrontal cortex (DLPFC), pre-supplementary motor area (pre-SMA), and OFC constitute the major targets of electrode montage for OCD [47]. This RCT will target the OFC, one of the primary brain regions engaged in OCD and disgust [48].

Each intervention will have two forms: active (real) and inactive (sham).

#### Active intervention

##### Real EC training

The EC task has been inspired by Kosinski’s research [28], who developed a brief game-like mobile app targeting body dissatisfaction. We have designed a computerized version with contamination-related stimuli for ten therapeutic sessions. We have set it in four difficulty levels, nearly the same as Kosinski. Our EC task will include 30 CS-US pairs using 30 contamination-related pictures as CSs and 30 pleasant pictures as USs.

In sessions 1 to 3 (difficulty level 1), ten pairs will be presented in each session. The task will consist of 4 blocks. Each of the first three blocks will start with a pair list shown on the screen at a time (including 3 pairs for the first block, 3 for the second, and 4 for the third one, a total of 10 pairs of pictures). The list will remain for 30s in the first two blocks and 40s in the third. Participants will be asked to memorize all the picture pairs. The subsequent trials will provide one of the CSs on the top of the screen and three US options on the bottom. Participants will be instructed to select the appropriate US as quickly and accurately as possible. Each pair will repeat 18 times in the first three blocks. Before starting the last block, there will be a rest time for 30s. Finally, the last block, including 60 trials, will review all 10 picture pairs with six repetitions each. The answer options will be presented 300 ms after the CS presentation starts and remain on the screen until the correct option is selected.

In sessions 4 to 6 (difficulty level 2), the answer options will remain for 400 ms and then disappear. Therefore, the participants should be more concentrated, find the correct answer, and memorize its location to choose after disappearing from the blank picture frame. The other components will be the same as before.

In each session of 7 to 10, 15 pairs will be practiced, with five pairs presented on the pair list of the first three blocks remaining for only 7 s to be remembered, and the subsequent trials will consist of 12 repetitions of each. The last block will include 60 trials reviewing all 15 pairs. The answer options will increase to 5, presented 300 ms after the CS presentation starts. For sessions 7 and 8 (difficulty level 3), the options will remain on the screen until selecting the correct answer. However, the options for sessions 9 and 10 (difficulty level 4) will be presented only for 400 ms.

The inter-trial interval (ITI) will be 1000 ms for all levels. Participants will answer to 240 conditioning trials in each training session which will take about 15 min to complete.

##### Real tDCS

Stimulation will be provided using the standard device (Activadose DC stimulator) with two rectangular saline-soaked sponge electrodes placed based on the international 10-20 electrode placement system. The cathode (size 5 × 7 cm^2^) will be placed over the left OFC (FP1) and the anode (size 10 × 10 cm^2^) over the right cerebellum (3 cm below the inion and 1 cm right of the midline). This montage is similar to that of Bation et al. [39], but increasing the size of the reference electrode (anode) is due to have a more focal cathodal effect over the left OFC. The tDCS will be delivered with the current intensity of 2 mA for 20 min for 10 sessions (5 days a week).

#### Inactive interventions

##### Sham EC training

For sham EC training, all the details will be the same as active EC training except that we will use nUSs instead of pUSs.

##### Sham tDCS

With the same device and electrode montage as active tDCS, the sham condition will include a current as low as 0.1 mA to be sure that current density is below the minimum threshold of modulating cortical activity, i.e., 0.017 mA/cm^2^ [46].

### Procedure

The enrolled candidate will be invited to an initial interview to confirm eligibility. They also will be provided with detailed information about the trial and procedure and then fill out written consent. Participants who will not meet the eligibility criteria or will not interested anymore will be excluded from the trial. The interview will continue with qualified volunteers in order to record demographic information such as age, gender, education level, age of onset, history of OCD in the family, taking medication or not (if yes, what, since when, and stability duration), and other receiving treatment (past and present) if any.

Participants will be encouraged not to be sleepy or hungry at all sessions in order to be able to focus on tasks appropriately. They will be informed to avoid these conditions in addition to smoking and caffeine consumption from the night before EEG recording.

Once participation is confirmed, an OCD patient will be assigned to one of four trial conditions based on a randomized allocation. A baseline assessment will consist of brain wave recording, computerized cognitive tests, and an online version of self-report measures; it will take about 60 min to complete. After that, as shown in the CONSORT diagram (see Fig. 1), all participants will complete a 10-session intervention. Each session will start with brain stimulation (sham or real); after 5 min, they will be asked to do EC training simultaneously.

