### Randomization and blinding

After screening for inclusion/exclusion criteria and obtaining informed consent, participants will assign to one of four arms through simple randomization with a 1:1:1:1 ratio using a blocked randomization list created by an online program (sealedenvelope.com) in the blocks of 4. The present study protocol is a single-blind design. The participants will be blind that one or both interventions are sham or active until the end of follow-up assessments. The principal investigator will be responsible for enrolment and assigning participants to interventions.

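### The protocol article gives conflicting orders for baseline testing and randomisation; on one of them, an exclusion criterion is applied after patients have been allocated

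*Protocol article*

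**What the plan says.** Four sections of the protocol article bear on the order of events.

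- **Procedure.** After the eligibility interview and consent, "Once participation is confirmed, an OCD patient will be assigned to one of four trial conditions based on a randomized allocation". The next sentence reads "A baseline assessment will consist of brain wave recording, computerized cognitive tests, and an online version of self-report measures", with a duration of about 60 minutes. The ten intervention sessions follow.
- **Participants.** The exclusion list opens with "The potential participants will be excluded if one or more of the following conditions are present" and ends with "invalid response on baseline tests".
- **Randomization and blinding.** "After screening for inclusion/exclusion criteria and obtaining informed consent, participants will assign to one of four arms". The same section says "The present study protocol is a single-blind design", describes only the participants as blind, and adds "The principal investigator will be responsible for enrolment and assigning participants to interventions".
- **Recruitment.** "Interested candidates will be invited to an initial meeting and baseline assessment within 3 days of enrollment". Assignment is not mentioned here.

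The Statistical analysis section commits to an intention-to-treat analysis of all subjects, with multiple imputation where data are missing.

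**The concern.** An exclusion for invalid baseline responses needs the baseline data. If patients already have an arm when those data are collected, part of the eligibility decision falls after randomisation. Three things are then at stake.

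1. **Selection after allocation.** Randomisation protects the comparison only for the patients it covers. A discretionary removal afterwards can differ between arms if the person deciding knows the arm, and the article sets out no safeguard against that.
2. **The analysis set.** Dropping a randomised patient for an invalid baseline is not compatible with an intention-to-treat analysis of all subjects.
3. **Numbers.** With four arms and 55 patients (55 / 4 = 13.75 per arm), each removal costs about 7% of an arm (1 / 13.75 = 7.3%) and upsets the balance of the blocks of 4.

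**Working it through.** **Order of events, section by section**

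| Section | Order stated or implied |
|---|---|
| Procedure | interview and consent → assignment → baseline described → sessions |
| Participants | baseline tests → validity judged → excluded or retained |
| Randomization and blinding | all inclusion/exclusion screening and consent → assignment |
| Recruitment | initial meeting and baseline named together; assignment not placed |

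Participants and Randomization and blinding fit together: if screening includes the baseline-validity criterion and precedes assignment, baseline must precede assignment. Procedure, read in the order it is written, places assignment before baseline. With the validity criterion in force, Procedure and Randomization and blinding cannot both be right.

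**Who makes the judgement**

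The article states that participants are blind and that the principal investigator both enrols and assigns. It does not say who decides that a baseline response is invalid, by what rule, at what point, or with what knowledge of the arm. The most that follows is that no stated safeguard exists.

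**How many patients could be affected**

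The plan has no figure on this point to reproduce. The article gives no rate of invalid baselines, so the rate r is an assumption. The 55 enrolled and 20% attrition come from Sample size.

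| Assumed r | Removed: 55 × r | Left: 55 × (1 − r) | Left after attrition: 55 × (1 − r) × 0.80 |
|---|---|---|---|
| 2% | 1.1 | 53.9 | 43.1 |
| 5% | 2.75 | 52.25 | 41.8 |
| 10% | 5.5 | 49.5 | 39.6 |

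That is about 1 to 6 patients. For comparison, the calculated requirement is 46, and 20% attrition alone leaves 55 × 0.80 = 44. The margin of 55 − 46 = 9 is intended for attrition, so removals for invalid baselines would compete with it.

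**Illustration only.** Take an arm of 14 with mean zero and remove two patients who each lie 1 SD above the mean. The remaining 12 average −2 / 12 = −0.17 SD. Nothing in the article links invalidity to a high score or to one arm, so this shows the sensitivity of a small arm and is not an estimate for this trial.

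**The case against.** The strongest reply is that the Procedure paragraph is loosely written and sets no order. The baseline sentence describes content and carries no time marker, and confirmed participation could include having passed every criterion. The exclusions are worded for potential participants, Recruitment ties baseline to the entry visit, and the section that governs randomisation puts screening first. The CONSORT flow chart and Table 1 might settle the matter, but their content is not visible in the text available. This largely stands: the intended order may well be baseline first, and the article cannot be said to fix the opposite. It does not remove the conflict, because a reader following Procedure as written would allocate first.

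A reader might go further and infer that the validity decision is made by someone who knows the arm. The single-blind design and the principal investigator's double role make that possible, but no section says so. A reader might also infer that the model covariates are collected by unblinded staff. The article does not support that: disgust sensitivity, anxiety and depression are self-reported on questionnaires, the self-report measures are completed online, and participants are blind.

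It can also be said that the commitment to intention to treat with imputation already covers the remedy. It does so in principle. However, the Participants section elsewhere removes enrolled patients from analysis (new prescriptions or other brain stimulation), so the article does not treat retention as absolute. How a randomised patient with an invalid baseline is handled should be stated.

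**Conclusion.** The point holds as an internal contradiction between Procedure, Participants, and Randomization and blinding. It does not establish that eligibility is in fact decided after randomisation. If the Procedure order is followed, one exclusion criterion is applied after allocation, with no stated protection from knowledge of the arm and against the intention-to-treat commitment. The extent is about 1 to 6 of 55 patients, resting entirely on an assumed rate of 2% to 10%. The direction and size of any bias cannot be derived from the article. It should be corrected, because the route to post-randomisation selection is avoidable and the arms are small.

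**What to change.** Amend the Procedure section to give one order, consistent with Participants and with Randomization and blinding: consent, eligibility interview, full baseline (EEG, cognitive tests, questionnaires), validity check against a rule set in advance, and only then allocation.

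The Trial status section says recruitment began in January 2023, so rewording cannot change how earlier patients were handled. For anyone already randomised before baseline, state that they remain in the intention-to-treat set, that an invalid baseline value is treated as missing and imputed under the existing multiple-imputation provision, and that the number of such cases is reported by arm.

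The cost is a change of sequence and wording, plus a short written validity rule. No visits or staff are added.
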